## Abstract

**Background:**

Currently all participants of the Dutch colorectal cancer (CRC) screening program with a positive faecal immunochemical test (FIT) are seen at the outpatient clinic to assess their health status, receive information on colonoscopy and CRC risk, and provide informed consent. However, for many patients this information could probably also safely be exchanged in an online setting, in order to reduce the burden for patients, healthcare system, and environment. In this study we will evaluate if a face-to-face pre-colonoscopy consultation can be replaced by a Digital Intake Tool (DIT) in a CRC screening population.

**Methods:**

This is a prospective multicentre single-arm, non-randomized study with a non-inferiority design. The DIT will triage a total of 1000 participants and inform them about CRC risk, colonoscopy, sedation, and provide bowel preparation instructions. Participants identified as high-risk (i.e., red-triaged) will be contacted by phone or scheduled for an appointment at the outpatient clinic. The primary outcome measure will be adequate bowel preparation rate, defined as the proportion of participants with a Boston Bowel Preparation (BBPS) score ≥ 6. To compare our primary outcome, we will use colonoscopy data from 1000 FIT positive participants who visited the outpatient clinic for pre-colonoscopy consultation. Secondary outcomes will include participation rate, colonoscopy adherence rate, patient experience in terms of satisfaction and anxiety, knowledge transfer, number of outpatient visits that can be averted by the DIT, and cost-effectiveness of the tool. Ethical approval was obtained from the Medical Ethical Committee of the Erasmus Medical Center (MEC-2021-0098).

**Discussion:**

This study aims to assess if a face-to-face pre-colonoscopy consultation can be replaced by an eHealth assessment and education tool in a FIT-based CRC screening program. In case favourable results are established, the intervention evaluated in this study could significantly impact CRC screening programs, benefiting both patients and healthcare systems on a (inter)national scale. Additionally, it would enable more personalized care as the DIT can be easily customized and made feasible in other languages, thereby enhancing healthcare accessibility.

**Trial registration:**

Dutch Trial Register: NL9315, date of registration: March 8th, 2021.

**Supplementary Information:**

The online version contains supplementary material available at 10.1186/s12876-023-03039-0.

## Introduction

### Colorectal cancer screening

Colorectal cancer (CRC) is the third most commonly diagnosed cancer worldwide and the second leading cause of cancer-related mortality [1]. CRC develops from a benign precursor lesion, detection and removal of these polyps prevent CRC, making it suitable for screening by decreasing both incidence and mortality. Therefore, CRC screening is recommended in countries where follow-up and treatment is accessible [2]. Over the past years many countries have introduced organized population-based screening programs, in European countries mostly using faecal immunochemical test (FIT) as the primary screening method [3]. In case of a positive FIT, participants are referred for a face-to-face consultation at the outpatient clinic before colonoscopy is carried out. Aim of this consultation is two-fold: assess participants’ health status and inform participants about CRC risk, colonoscopy including potential complications, sedation and bowel preparation. Both are necessary to achieve a well-informed shared decision.

The increasing burden on outpatient clinics highlights the need for healthcare providers and patients to adopt a more home-based approach to healthcare. Digital health offers a feasible solution, allowing patients to receive care without the need for in-person visits. This not only reduces the burden on the outpatient clinic, but it also offers several benefits for patients as it enables them to receive care at home. In the context of CRC screening, alternatives to the face-to-face pre-colonoscopy consultation for FIT positive participants must be explored. However, it is essential to ensure that these alternatives do not negatively impact important performance indicators of the CRC screening program such as adherence to colonoscopy, bowel cleanliness, or patient experience.

As medical health is undergoing a digital transformation, a lot of research focusses on digital patient education. Bowel preparation is a complex process, and clear instructions are necessary to obtain optimal bowel preparation quality. Currently, a verbal explanation combined with written instructions are standard of care [4]. However, studies have shown that various patient education tools, such as videos and smartphone education, improve bowel preparation and patient satisfaction [5–8]. We can conclude that such education tools could be used before colonoscopy is carried out. However, informing FIT-positives includes more than bowel preparation instructions. Also, information regarding the FIT positive result, CRC risk, and colonoscopy is of high importance and should be provided before colonoscopy is carried out. Before the national CRC screening program was implemented in the Netherlands, Stoop et al. compared face-to-face with telephone pre-colonoscopy consultations in a CRC screening population. They found that colonoscopy adherence and patient satisfaction were lower in the telephone consultation patient group compared to the face-to-face group. The quality of bowel preparation did not differ [9]. Therefore, currently a visit at the outpatient clinic is standard of care for FIT positive participants in the Netherlands.

Besides providing information, FIT-positives’ health status is evaluated during the pre-colonoscopy consultation. Veldhuijzen et al. developed and evaluated a computer-based education pre-colonoscopy tool that is able to triage patients who are referred for colonoscopy. The tool appeared to be equally effective as nurse counselling in terms of bowel preparation, increased adherence to colonoscopy and satisfaction among patients that received the computer-based education modality [10]. However, it is important to note that this randomized controlled trial was performed in a non-screening population, and all included participants had already been triaged and referred for colonoscopy. FIT positive individuals differ from symptomatic patients as they are referred for colonoscopy without having seen a medical professional who has established the participant’s health status and obtained informed consent. Therefore, these results cannot be generalized to a population participating in CRC screening.

Thus far, no data is available on the use of an eHealth tool in a patient population who has not been seen or informed by a medical professional before undergoing an invasive intervention, like a colonoscopy. This study will evaluate the effectiveness and patient experience of a Digital Intake Tool (DIT), that replaces the face-to-face pre-colonoscopy consultation from a hospital setting to home within a FIT-based CRC screening population.

## Methods and analysis

### Aim

The aim of this study is to determine if a face-to-face pre-colonoscopy consultation visit can be replaced by an eHealth tool performed at home in a FIT-based CRC screening program.

### Primary outcome

Adequate bowel preparation is an important quality parameter for colorectal cancer screening programs. Poorly cleaned colons can lead to suboptimal detection of lesions, necessitating repeat colonoscopies. Therefore, the primary outcome of this study is the quality of bowel preparation classified by BBPS. Patient-related factors associated with poor bowel cleaning, for example obstipation, will be collected at baseline.

### Secondary outcomes

Secondary outcomes include participation and response rate, colonoscopy adherence and the number of outpatient visits that are avoided by DIT. The DIT will be evaluated in terms of safety: “Are participants correctly classified as low risk?”, knowledge transfer and usability of the application. Also patient experience will be assessed in terms of satisfaction and anxiety levels both before and after completion of the DIT. Lastly, cost-effectiveness will be assessed.

### Study design

This is a prospective, multicentre cohort study with a non-inferiority design to assess the effectiveness of a pre-colonoscopy eHealth tool in participants of a FIT-based CRC screening program. Study sites are located in the Netherlands, and include an academic hospital, regional hospitals, and endoscopy centres. In this single-arm study, all enrolled participants will receive the DIT intervention instead of standard counselling at the outpatient clinic. For analyses of our primary outcome, we will compare colonoscopy data of the study participants with that of 1000 FIT positive participants who received pre-colonoscopy counselling at the outpatient clinic of endoscopy centres that did not participate in the DIT-trial (Fig. 1). Additionally, we will assess patient-related outcome measures, including anxiety levels, satisfaction and knowledge transfer among a reference cohort consisting of 100 FIT-positive participants who received pre-colonoscopy counselling at the outpatient clinic. This study was designed according to the Standard Protocol Items: Recommendations for Interventional Trials (SPIRIT) 2013 shown in Supplementary Table 1.

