### Study setting: Dutch CRC screening program

In the Netherlands, a national CRC screening program was gradually implemented in 2014, using biennial FIT. All individuals between the age of 55 and 75 years old receive an information leaflet with information on CRC, FIT, advantages and disadvantages of CRC screening enclosed with a FIT. Participation and returning FIT is free of charge. In case of a positive FIT, colonoscopy is recommended. FIT positive participants receive, by mail, the result of their stool test together with an invitation for a pre-colonoscopy consultation at the outpatient clinic of a certified endoscopy centre. Once both the medical professional and the patient have agreed to proceed with screening colonoscopy, detailed information on bowel preparation is provided during the pre-colonoscopy consultation, and colonoscopy is scheduled within a three-week timeframe. Reasons not to schedule screening colonoscopy are a life expectancy of less than five years and FIT positive individuals who are unable or unwilling to undergo colonoscopy [11]. Each year around 2.2 million individuals are invited to participate in the national CRC screening program, approximately 70% return their FIT of which 4–5% have a positive FIT. As a consequence, approximately 70.000 participants are referred to the outpatient clinic annually [12].

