### Sample size calculation

A sample size calculation was performed for demonstrating non-inferiority of the DIT versus all participants visiting the outpatient clinic with regard to the primary endpoint; adequate bowel preparation, defined as a Boston Bowel Preparation Score (BBPS) of 6 or higher. The choice of non-inferiority design was motivated by the expectation that the DIT will improve secondary outcomes regarding costs and satisfaction. According to the Dutch national CRC screening organization at least 90% of all participants in the CRC screening program must have a BBPS of at least 6. Based on earlier data, currently in 97.5% a BBPS of 6 or higher is achieved among participants of the Dutch screening program. With a clinically acceptable difference of -0.5%, corresponding to at least 89.5% of participants achieving adequate bowel preparation, the non-inferiority margin is set at -8.0%. To achieve 90% power with a one-sided Exact test at a 2.5. significance level, 738 participants are needed. Anticipating 30% loss to follow-up or withdrawal of participants, we aim to include 1000 participants.

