### Data collection

Demographic data and patient experiences will be collected via the DIT and will be stored in the electronic data management system, Castor Electronic Data Capture. Each participant will receive a unique study number after study enrolment. This study number will be used for all study documentation. Colonoscopy data will be reported by the gastroenterologist who performed the colonoscopy. This data is stored in the national database of the Dutch screening organization, Screen-IT. By linkage to Screen-IT we will retrieve the following colonoscopy data: BBPS, caecal intubation, reason for incomplete colonoscopy, American Society of Anaesthesiologists physical status classification (ASA), Gloucester Comfort Score and re-colonoscopy due to inadequate bowel preparation or incomplete colonoscopy. In addition, colonoscopy data will be retrieved from 1000 FIT-positive participants of the CRC screening program who did not participate in the DIT-trial. This will allow us to compare the DIT intervention to face-to-face consultation at the outpatient clinic with regard to our primary outcome.

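### The comparator is fixed at 1000 retrieved records although the available pool is probably far larger: an avoidable loss of precision, not an error

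*Protocol article*

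**What the plan says.** The Abstract, Study design and Data collection sections all give the same comparator size. Study design says that "we will compare colonoscopy data of the study participants with that of 1000 FIT positive participants" who had outpatient counselling at centres outside the trial. Data collection says that "colonoscopy data will be retrieved from 1000 FIT-positive participants of the CRC screening program who did not participate in the DIT-trial".

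On the source, Data collection describes the colonoscopy reports thus: "This data is stored in the national database of the Dutch screening organization, Screen-IT". It names linkage to that database for the trial participants. For the comparators it says only that data will be retrieved, so Screen-IT is a fair inference but is not stated.

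On the size of the pool, the Study setting section says that "approximately 70.000 participants are referred to the outpatient clinic annually".

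The Sample size section contains one calculation: "To achieve 90% power with a one-sided Exact test at a 2.5. significance level, 738 participants are needed". It continues: "Anticipating 30% loss to follow-up or withdrawal of participants, we aim to include 1000 participants". It gives no separate calculation or precision target for the comparator. Statistical analysis judges non-inferiority on the lower limit of a two-sided 95% interval for the observed difference and mentions no adjustment. The Discussion concedes that selection bias may be present.

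**The concern.** When one group must be recruited and the other only extracted, there is usually little reason to keep them the same size. The comparator's sampling error goes into the primary interval just as the DIT group's does, but it can be reduced without approaching a patient.

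Two things are at stake. The first is the width of the primary interval. The second is support for adjustment. The comparison is not randomised, and events (inadequate preparations) are few when about 97.5% of preparations are adequate. A larger comparator gives an adjusted analysis more to work with.

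**Working it through.** **Inputs.** Reference rate: the Sample size section says that "currently in 97.5% a BBPS of 6 or higher is achieved". DIT group: 1000 enrolled with 30% loss leaves 1000 × 0.70 = 700 evaluable; 1000 evaluable is used as the upper case. Comparators: 1000, all assumed evaluable. National pool: the Study setting figures give 2.2 million × 0.70 × 4% to 5% = 61,600 to 77,000 a year, which agrees with the stated 70,000. These are referrals at all centres, not records with a bowel preparation score at non-participating centres.

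**The plan's own figure.** There is no calculation for the 1000 comparators to reproduce. The 738 for the trial does not follow from 97.5% and a margin of 8 points. The two-group formula gives (1.96 + 1.2816)² × 2 × 0.975 × 0.025 / 0.08² ≈ 80.04, so 81 per group (105 with continuity correction). An exact one-sample test of 89.5% against 97.5% needs 95 to 108. So 738 gives no basis for a comparator of 1000.

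**Share of variance.** With equal rates, the variance of the difference is proportional to 1/700 + 1/1000 = 0.001429 + 0.001000 = 0.002429. The comparator supplies 0.001000 / 0.002429 = 41%.

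**Half-width and power.** Half-width = 1.96 × √[0.975 × 0.025 × (1/n_DIT + 1/n_ref)]. For 700 and 1000 this is 1.96 × √(0.024375 × 0.002429) = 1.96 × 0.007694 = 1.508 points. Power with equal true rates = Φ(margin/SE − 1.96).

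| Comparators | Half-width, 700 DIT (points) | Half-width, 1000 DIT (points) | Power at 0.5 points, 700 DIT |
|---|---|---|---|
| 1000 | 1.508 | 1.368 | 9.5% |
| 2000 | 1.344 | 1.185 | 10.9% |
| 5000 | 1.235 | 1.060 | 12.2% |
| 10,000 | 1.196 | 1.015 | 12.7% |
| unlimited | 1.157 | 0.968 | 13.3% |

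With 700 evaluable, going from 1000 to 5000 comparators narrows the interval by 1 − 1.235/1.508 = 18%. The most that any comparator could achieve is 1 − 1.157/1.508 = 23% (29% with 1000 evaluable), because the DIT group sets the floor. Most of the gain is reached by 5000.

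**At the two margins in the article.** At 8 points, 0.08/0.007694 − 1.96 = 8.4, so power exceeds 99.99% with 1000 comparators and cannot usefully rise. At 0.5 points, even an unlimited comparator gives only 13.3% (17.2% with 1000 evaluable). For 90% power there, about 10,245 evaluable DIT participants would be needed.

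**Events available for adjustment.** At 2.5% inadequate, 1000 comparators supply about 25 events and 700 DIT participants about 17 or 18, roughly 42 in all. With 5000 comparators, the comparator alone supplies about 125.

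**The case against.** The strongest reply is that nothing here is wrong. The figure is the same wherever it appears, it matches the planned enrolment, and a comparator of equal size is an ordinary choice. The verdict at either margin barely moves. The article condenses a fuller protocol, so a reason for 1000, such as an access agreement, fees or data minimisation, may be recorded there. All of this stands, and it limits the point to a suggestion about efficiency.

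The main threat is also bias rather than precision: more records would put a tighter interval around a difference that may still be biased. That stands for unmeasured preference for eHealth. It does not remove the value of more records for adjusting on what is measured.

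Three stronger readings should be resisted:

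- A reader might infer that the cap leaves the trial underpowered. At 8 points power is already nearly complete, and at 0.5 points the shortfall comes from the margin and the DIT group.
- Power against an intermediate deficit, such as 2 points, would show a larger gain, but no such margin appears in the article.
- A reader might suppose that the comparators come from only a few centres. The article does not say how many there are.

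**Conclusion.** The point holds as a minor, avoidable inefficiency. Using 5000 comparators instead of 1000 would narrow the primary interval by about 18%, from 1.508 to 1.235 points, and raise the expected comparator events from about 25 to about 125.

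This rests on 97.5% in both groups, 700 evaluable DIT participants, independent observations and a usable pool well above 1000. The last is likely from the national figures but is not stated. Clustering by centre would reduce the gain, particularly if extra records came from the same centres, so the 18% is a best case.

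The documents do not support calling the figure of 1000 a mistake or saying that it endangers the primary conclusion. The two conflicting margins, 8.0 points under Sample size and 0.5 points under Statistical analysis, matter more and must be reconciled separately.

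**What to change.** In the Abstract, Study design and Data collection sections, replace the fixed 1000 with all eligible face-to-face records from non-participating centres within a calendar window to be defined. The article states no window for the comparators; the DIT inclusion period (October 2021 to the anticipated March 2024) is one candidate. If access is limited, ask for several thousand records spread over many centres, or state the reason for 1000. Taking every eligible record in the window also removes any discretion over which 1000 are drawn.

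In Statistical analysis, use these records for a primary difference adjusted for measured factors such as age, sex and ASA class. Individual centre cannot be an adjustment factor, because Study design takes the comparators from centres outside the trial and so centre and group do not overlap. The report should say that unmeasured preference for eHealth remains.

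The cost is a larger data request, a possible access fee, a data-minimisation justification and the wording changes. No further patient is enrolled. The article describes the retrieval as still to come.

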### Sample selection

All FIT-positive participants of the Dutch CRC screening program are eligible for inclusion if they are able to provide informed consent. Patients are excluded when having 1) a visual disability 2) lack of internet access or do not have a relative with internet access 3) Dutch illiteracy. FIT-positives are requested to contact the outpatient clinic of the endoscopy centre they have been referred to, prior to their scheduled face-to-face consultation. Patients will be recruited during this phone contact. If they choose to have a face-to-face visit instead of the DIT intervention, they will not be included in the study.

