### Statistical analysis

Continuous data will be summarized using means and standard deviations, or medians and interquartile ranges in case of skewed distributions. Categorical data will be presented in relative frequencies and counts. Comparison of normally distributed continuous variables will be done with the Student t-test or Mann-Whitney U test in case of skewed distributions. Categorical outcomes will be analysed using χ2 test. Non-inferiority of our primary outcome will be evaluated by whether the lower bound of the two sided 95% confidence interval of the observed difference in adequate bowel preparation rate is above the non-inferiority margin of 0.5%.

For repeated measurements within participants, e.g. the total STAI-6 score before and after the DIT, paired tests will be used to analyse differences. Differences are considered significant in case *p* ≤ 0.05. Other secondary outcome parameters will only be obtained from study participants who underwent the DIT intervention, these results will be reported using descriptive statistics.

Statistical analysis will be performed using IBM SPSS statistics.

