It is known that individuals from ethnic minority groups are difficult to reach, especially in a CRC screening setting [24, 25]. Many of the ethnic minority groups living in the Netherlands have a poor understanding of the Dutch language and lower (health) literacy. Therefore, a limitation of this study is that non-Dutch speakers are excluded. For participation in studies, patients need to be able to read and understand the patient information form in Dutch and sign for informed consent to participate in the DIT-trial. However, in case the study shows favourable results, the DIT can easily be adapted to support additional languages. Follow-up studies should still be carried out to validate the DIT among non-Dutch speakers. However, in addition to language barriers, ethnic minority groups often experience a lower socioeconomic status (SES) [24]. In this study we will be able to evaluate the DIT among participants from different socioeconomic backgrounds, low SES serving as an approach to ethnic minority groups, based on postal code. A second limitation is the recruitment process of the study. Because of the non-randomized study design, selection bias may be present. To stay in line with the current logistics and regulations of the Dutch CRC screening program, we are unfortunately unable to conduct a randomized controlled trial. Consequently, it is possible that only individuals who prefer eHealth over regular care will be included. Nevertheless, we will collect all reasons given by non-participants refraining from participation. This will help to gain more insight into the public’s attitude and preferences towards digitalization of this process.

In conclusion, in this study we will evaluate if pre-colonoscopy outpatient visits can be replaced by an eHealth tool for FIT positive participants of the Dutch CRC screening program.

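### The primary non-inferiority decision rests on a crude difference between self-selected DIT users and patients from other centres, so patient selection and centre differences enter the estimate as DIT effect

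*Protocol article*

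**What the plan says.** **Intervention group.** Sample selection in the protocol article admits FIT-positives able to consent. It excludes visual disability and "lack of internet access or do not have a relative with internet access 3) Dutch illiteracy". It then adds a preference filter: "If they choose to have a face-to-face visit instead of the DIT intervention, they will not be included in the study".

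**Comparator.** Study design takes 1000 FIT-positives who were counselled "at the outpatient clinic of endoscopy centres that did not participate in the DIT-trial". Data collection describes them more loosely as "1000 FIT-positive participants of the CRC screening program who did not participate in the DIT-trial". Neither section applies the DIT eligibility criteria to them or names matching.

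**Decision rule.** Statistical analysis asks whether the "lower bound of the two sided 95% confidence interval of the observed difference in adequate bowel preparation rate" lies above the margin, and assigns categorical outcomes to a χ2 test. No covariate, weighting or matching is named.

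**Acknowledgement.** The Discussion states: "Because of the non-randomized study design, selection bias may be present". It says that randomisation was not possible within the screening programme and that non-participants' reasons will be collected. Centre differences are not discussed.

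**The concern.** The two groups differ in at least three ways besides the DIT. One was filtered for sight, internet access and Dutch literacy. The same group preferred a digital route. And under Study design no centre supplies both groups, so local preparation practice and endoscopists' BBPS scoring are completely confounded with the intervention. A crude difference attributes all of this to the DIT.

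In a non-inferiority study the direction matters: if the DIT group would have prepared better under any form of counselling, a real loss from the DIT is partly hidden. The confidence interval covers sampling error only and gives no warning. This contrast carries the study's main claim, that the tool can replace the visit.

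**Working it through.** The plan gives no figure for the bias, so there is none to reproduce. The check asks how large selection bias could be and what it would do to the decision.

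**Inputs from the protocol article**
- Reference adequate-preparation rate: 97.5% (Sample size calculation).
- Margins: 8.0 points (Sample size calculation) and 0.5 points (Statistical analysis; printed without a sign, read here as -0.5).
- Comparators: 1000. DIT participants: 1000 enrolled, 738 required; 1000 × 0.7 = 700 remain after the anticipated 30% loss.

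**Assumed, not in the documents**
- x, the share of comparators who would have been ineligible for the DIT or declined it: 5% to 20%.
- d, the amount by which their adequate-preparation rate is lower: 5 to 15 points.

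**Step 1: size and ceiling of selection bias.** If all comparators together have rate 97.5%, the DIT-like ones among them have rate 97.5 + x·d, and the crude difference is biased by x·d in the DIT's favour.
- Low end: 0.05 × 5 = 0.25 points.
- High end: 0.20 × 15 = 3.0 points. This would put DIT-like comparators at 100.5%, which is impossible.
- The ceiling is 100 - 97.5 = 2.5 points, reached only if every inadequate preparation fell among people who would not have used the DIT.

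The usable range is 0.25 to 2.5 points.

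**Step 2: precision.** Half-width = 1.96 × √[0.975 × 0.025 × (1/700 + 1/1000)] = 0.0151, or 1.51 points. The upper part of the bias range exceeds it.

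**Step 3: effect on the decision.** With true difference Δ, bias b and margin m (as a positive number), the chance of declaring non-inferiority is about Φ[(Δ + b + m)/SE - 1.96]. Here SE = √[pC(1 - pC)/1000 + pT(1 - pT)/n], pC = 0.975 and pT = 0.975 + Δ + b. With Δ = -m, every such declaration is false, and the nominal rate is 2.5%.

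Example: m = 0.005, Δ = -0.005, b = 0.01, n = 1000. Then pT = 0.98, SE = √(0.000024375 + 0.0000196) = 0.00663, and Φ(0.01/0.00663 - 1.96) = Φ(-0.45) ≈ 33%.

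Ranges below are for n = 738 to 1000.

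| Bias (points) | False non-inferiority, 0.5-point margin | False non-inferiority, 8-point margin |
|---|---|---|
| -1.0 | about 0.1% | 0.2–0.3% |
| 0 | 2.5% | 2.5% |
| +0.25 | about 5% | about 4% |
| +0.5 | 10–11% | 6–7% |
| +1.0 | 29–33% | 13–16% |
| +1.5 | 61–67% | 25–31% |
| +2.0 | 90–93% | 42–51% |
| +2.5 (ceiling) | over 99% | 61–71% |

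With the 8-point margin and a true difference between 0 and -2 points, the probability of non-inferiority is above 99.9% for every bias from -1 to +2.5 points.

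**Step 4: can the planned data repair it?** The Screen-IT items listed in Data collection include ASA class but not age, sex, socioeconomic status or obstipation. Age and sex of decliners (Participation rate) and postcode-based status (Discussion) concern people approached or enrolled at DIT centres, not the comparators. A centre term cannot be estimated separately from treatment when no centre contributes to both groups.

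**The case against.** The authors disclose the selection bias and explain why they could not randomise. They also do more than record reasons for declining: they collect age and sex of non-participants, report the participation rate, examine socioeconomic background and record risk factors for poor cleansing. A fuller protocol or SAP, not shown, may specify adjusted analyses.

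Much of this stands. But these measures describe the selection; none corrects the estimate. And although the article never uses the word unadjusted, the decision rule it publishes is the observed difference. The criticism is of that rule, not of missing detail.

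Four stronger readings are tempting and are not supported:
- **The DIT group is healthier, so the result must favour non-inferiority.** Sample selection has no health exclusion, a relative's internet access is enough, and high-risk (red-triaged) participants stay in the study. That selection favours the DIT is plausible inference. The direction of centre differences is unknown.
- **The bias could be 3 points or more.** Selection bias in the DIT's favour is capped at 2.5 points by the plan's own 97.5%.
- **The verdict is unsafe under either margin.** Under 8 points it is unsafe only if the true deficit is near 8.
- **Study design and Data collection contradict each other.** They are compatible: patients of non-participating centres are also people outside the trial. The second description is merely looser, and read alone would admit decliners at DIT centres.

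**Conclusion.** The concern holds. The primary estimate mixes the DIT effect with patient selection and with centre, and the plan as published has no step that separates them. The amount is unknown because x and d are assumptions. Selection could add anything up to 2.5 points in the DIT's favour, and centre differences could add to or offset it.

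Whether this changes the decision depends on which of the two stated margins applies, and that conflict must be reconciled in its own right. Under 0.5 points, a bias of 1 point raises false non-inferiority at the margin from 2.5% to about 29–33%, and 2 points raises it to 90–93%. Under 8 points, the decision is robust unless the true deficit is close to 8, although the point estimate and interval remain biased. These probabilities rest on a normal approximation, a 97.5% comparator rate and a bias that adds to the true difference.

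**What to change.** 1. Prespecify as primary a standardised (g-computation) or propensity-weighted risk difference, adjusted for covariates available in both groups: ASA class from Screen-IT, plus age, sex and postcode-based socioeconomic status if they can be obtained for comparators. Confirm that availability first. Report the crude difference second.
2. As a sensitivity analysis, add Screen-IT comparators from the participating centres before inclusion began in October 2021. This gives a within-centre contrast. State that it is confounded with calendar time and does not by itself remove self-selection.
3. State that patient-level adjustment cannot remove residual centre confounding, and limit the conclusion accordingly.
4. Align the comparator description in Data collection with that in Study design.

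Pooling DIT users with decliners is not a substitute: it dilutes any harm from the DIT, which is anti-conservative for non-inferiority, and leaves centre differences in place.

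Cost: a somewhat larger data extract with its access administration, modest analysis work and a slightly wider confidence interval. No new patients or procedures are needed.
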